## Methods

### Study design

We will conduct a randomized, controlled intervention field study employing a pretest–posttest design to compare the effects of 30-min walks in urban built environments and forests with different road traffic noise levels. Healthy adults will be asked to go for a guided group walk with a maximum of six participants. The participants will be randomly assigned to one of the following conditions: urban built environment with high road traffic noise, urban built environment with low road traffic noise, forest with high road traffic noise, and forest with low road traffic noise. A fifth condition will be a walk in a forest with low traffic noise, in which participants walk with a mindfulness intervention. In this study protocol, we focus on the examination of the objective environmental factors, as noted above, and the last condition is not discussed here (above RF2). Data will be assessed before (t1) and directly after (t2) the walk. After this, participants will be instructed to walk individually three times during the subsequent 10 days. Ten days after participating in the field experiment, participants will receive an invitation to respond to a third questionnaire (t3). The third measurement point is only used for RF2 and is not included here; as for answering the research questions included in this study protocol, we focus only on measurement timepoints t1 and t2.

### Research questions and hypotheses

#### Research question RQ1

Compared to walking in an urban built environment, does walking in a forest lead to a stronger increase in stress reduction (variable 1), restoration (variable 2), positive affect (variable 3), attention (variable 4), nature connectedness (variable 5), and rumination (variable 6) as well as a stronger decrease in negative affect (variable 7)?

#### Hypothesis H1

Compared to walking in an urban built environment, taking a walk in a forest leads to a stronger increase in stress reduction (1), restoration (2), positive affect (3), attention (4), nature connectedness (5), and rumination (6) as well as a stronger decrease in negative affect (7).

#### RQ2

Compared to walking in an environment with high traffic noise, does walking in an environment with low traffic noise lead to a stronger increase in the outcome variables 1–6 as well as a stronger decrease in negative affect?

#### H2

Compared to walking in an environment with high road traffic noise, taking a walk in an environment with low road traffic noise leads to a stronger increase in the outcome variables 1–6 as well as a stronger decrease in negative affect.

#### RQ3

Compared to walking in a forest with high road traffic noise, does walking in a forest with low road traffic noise lead to a stronger increase in the outcome variables 1–6 as well as a stronger decrease in negative affect?

#### H3

Compared to walking in a forest with high road traffic noise, taking a walk in a forest with low road traffic noise leads to a stronger increase in the outcome variables 1–6 as well as a stronger decrease in negative affect.

#### RQ4

Compared to walking in an urban built environment with high road traffic noise, does walking in an urban built environment with low road traffic noise lead to a stronger increase in the outcome variables 1–6 as well as a decrease in negative affect?

#### H4

Compared to walking in an urban built environment with high road traffic noise, taking a walk in an urban built environment with low road traffic noise leads to a stronger increase in the outcome variables 1–6 as well as a stronger decrease in negative affect.

#### RQ5

What is the effect of 30-min walks in the forest on outcome variables 1–6 compared to walking in urban built settings, depending on the noise in the settings?

### Procedures

The field experiment is based on a between-subject design, and assessments consist of self-report questionnaires, physiological measures, an attention test, and objective noise measurements. In preparation for the main data collection, a pretest was conducted in February and March 2022 to test the questionnaire and determine if changes in the experimental procedure were required. The questionnaire and experimental procedure were adjusted in line with the outcomes of the pretest.

Walking sessions will take place between 2:00 p.m. and 5:30 p.m., since participants’ salivary cortisol levels will be assessed, and salivary cortisol levels have been shown to fluctuate systematically during the day [60–62]. Additionally, stronger mental fatigue during the daytime is assumed [63] and hence, a higher need for restoration [64].

Before participation, individuals will be given a short introduction to the research topic, their task in the experiment, privacy policies, and asked to give their written informed consent. Before the date of participation, individuals will be asked to refrain from consuming caffeine and from performing exhausting physical activity 2 h before their walking appointment. Furthermore, participants will be requested to refrain from going for a walk on the day of their walking appointment before their participation and not to consume any drugs 24 h before taking the walk.

Upon arrival at the test site, the participants’ salivary cortisol levels will be assessed to obtain a baseline stress level. Next, participants will complete a series of questionnaires. After this, participants will be equipped with wearable wristbands to assess their skin conductance during the walk. Then, the participants’ attention will be assessed using the Necker Cube Pattern Control Test [65, 66]. Before starting the walk, a 2-min baseline value of participants’ skin conductance will be obtained while the individuals are seated, and a second salivary cortisol probe will be taken directly before the walk starts. One of the two experimenters present in the test setting will then lead the participants at a moderate pace of around 4,7 km/h along a predetermined route. The second experimenter will stay at the starting point of the route and look out for the assessment devices. Skin conductance will be measured continuously during the walk. Furthermore, during every walk, the experimenter will measure the sound while walking about 6 m ahead of the participants. A sound level meter (XL2 by NTI Audio, Schaan, Liechtenstein) with a free-field measurement microphone, fulfilling class 1 environmental requirements according to IEC 61672, will be used. The microphone will be fixated onto a recording stick and carried in a backpack during the walk by the experimenter, resulting in a microphone height of approximately 1.7 m above the ground (see Fig. 1).

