**Fig. 1 Fig1:**
[figure not shown]
Audio recording

Participants will be asked to walk in silence and not to outpace the experimenter. After the walk, a third cortisol probe will be taken, the attention test will be conducted again, and participants will be asked to respond to the post-questionnaire. For an illustration of the study procedure, see Fig. 2.

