### Outcomes

#### Primary outcomes

The primary outcomes are “perceived restoration”, measured with a self-report questionnaire and salivary cortisol as a physiological stress marker.

Perceived restoration will be assessed using a slightly modified version of the restoration outcome scale (ROS) [67]. The questionnaire was put in past tense, and participants will be asked to what extent the walk contributed to three items concerning relaxation and calmness (e.g., “I feel calmer after being here”), one item reflecting attention restoration (“my concentration and alertness clearly increased”), and two items indicating clearing one’s thoughts (e.g., “I was able to forget my everyday worries here”). The questionnaire has been translated into German, including a back translation into English by the internal translator of the Swiss Federal Research Institute WSL. Items are rated on a Likert scale ranging from 1 (*not at all*) to 7 (*completely*). The scale has been used in several previous studies examining the benefits of exposure to nature [14, 68, 69] and has been shown to have good internal consistency with a Cronbach’s alpha of .92 [67].

The physiological stress marker salivary cortisol is considered a reliable indicator for assessing hypothalamic pituitary adrenocortical (HPA) axis activity [62, 70]. Saliva samples will be collected using synthetic swabs (Sarstedt, Germany). For saliva collection, participants will place the swab in their mouth for 2 min before returning it to the salivette collection tube. The salivettes will be put in a portable cooler immediately after saliva collection and stored there until the end of the walk. When returning from the field, saliva samples are frozen and stored at − 20 °C until analysis. The samples will be analyzed by the laboratory of [name]. [name] at the Technical University of Dresden, Germany, to determine cortisol levels. After thawing, the samples will be centrifuged at 3,000 rpm for 5 min to obtain a clear supernatant of low viscosity. Salivary concentrations are measured using a commercially available chemiluminescence immunoassay with high sensitivity (Tecan – IBL International, Hamburg, Germany; catalog number R62111).

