### Data processing and statistical analysis

We will analyze research questions 1–5 using linear mixed-effects models. We will conduct prespecified models comparing the change from t1 to t2 in the outcome measures between participants in the different conditions. Prior to the analyses, the distributions of all measures will be examined, and data will be checked for influential outliers. The model diagnostics of linear mixed-effects models will be examined to assure that model assumptions are met. Due to the large number of outcome variables and the distinct theoretical background of the outcome variables regarding exposure to nature, the results will be analyzed and published in separate papers. One paper will focus on restoration, stress, attention, and affect. A second paper will focus on rumination.

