In both models, we will specify fixed effects for conditions (vegetation and noise) and time (before and after the walk). Further, we will include an interaction term between vegetation and noise, as well as a random intercept term accounting for individual differences (one per subject). Additionally, in both models, the group constituting the experimental unit in this study will be entered as a second random intercept (one per group) to account for the hierarchical structure of the data due to the organization of participants into different groups. Since we will be conducting group walks, individuals will be subsamples of the walking groups, and the treatment will be applied to groups, not to individual participants. Therefore, the following model will be used: $$outcome \sim vegetation\times noise (1 |\mathrm{ group}/\mathrm{ subject})$$. If suitable, further exploratory models will be computed. For all analyses, we will set the significance level at .05 and analyses will be conducted with R [100] and R package lme4 [103].

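### Co-primary cortisol has two pre-walk samples, but the plan does not say which is the before value and calls only the one taken before the test battery a baseline

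*Protocol article*

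**What the plan says.** The protocol article, Primary outcomes, names perceived restoration and cortisol as primary: "measured with a self-report questionnaire and salivary cortisol as a physiological stress marker".

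Procedures sets out three saliva samples:
- On arrival at the test site, "salivary cortisol levels will be assessed to obtain a baseline stress level".
- After the questionnaires, wristband fitting, attention test and a 2-minute seated skin-conductance reading, "a second salivary cortisol probe will be taken directly before the walk starts".
- "After the walk, a third cortisol probe will be taken", ahead of the repeat attention test and the post-questionnaire.

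The analysis has two time points. Study design: "Data will be assessed before (t1) and directly after (t2) the walk". Data processing and statistical analysis promises prespecified models "comparing the change from t1 to t2 in the outcome measures between participants in the different conditions" and adds that "we will specify fixed effects for conditions (vegetation and noise) and time (before and after the walk"), with a "random intercept term accounting for individual differences (one per subject") and another for walking group. One model is given for all outcomes. No sentence says which pre-walk cortisol sample is t1, or whether both enter.

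**The concern.** The hypotheses concern the 30-minute walk, but the label baseline is attached to a sample taken before a test battery that precedes the walk. An analyst following the label would measure battery plus walk. One following the t1/t2 wording would probably choose the sample directly before the walk. A third might pool or average the two. All three fit the text, and they need not give the same answer.

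This is a co-primary outcome, so the choice should not be open once data can be seen. By the article's own dates, two of the three collection waves (May–October 2022 and August–October 2023) ended before registration on 23.11.2023. The article does not say whether any cortisol results were known by then.

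**Working it through.** **Inputs.** The sampling order comes from Procedures and the time factor from Data processing and statistical analysis. The protocol gives no cortisol standard deviation, effect or correlation. Its power calculation (19 groups) is for the restoration outcome scale only, so there is no cortisol figure to reproduce. All correlations below are assumed. Variances are per person in units of σ², without the group component.

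**1. What each baseline measures.** Let the battery shift cortisol by b, carried through to the post-walk sample, and let the walk shift it by w. The within-condition change is then:
- from arrival: w + b
- from the sample directly before the walk: w
- from the mean of the two: w + b/2

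Take b = +0.4 and w = −0.3 (illustrative). The results are +0.10, −0.30 and −0.10, so the arrival baseline reverses the sign. A simulation with these values gave +0.097, −0.304 and −0.103.

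**2. Contrasts between conditions.** If b is the same in every condition it cancels. In the same simulation, with a true environment × time contrast of −0.30, the estimates were −0.287 (arrival), −0.292 (pre-walk) and −0.290 (mean). If b differs by δ between conditions, the change-score contrasts become walk + δ, walk, and walk + δ/2.

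**3. Precision.** Let r₁₂, r₁₃ and r₂₃ be the correlations of arrival with pre-walk, arrival with post-walk, and pre-walk with post-walk.
- Change from one sample: 2(1 − r), with r its correlation with post-walk
- Change from the mean of both: 1 + (1 + r₁₂)/2 − (r₁₃ + r₂₃)
- One covariate: 1 − r²
- Both covariates: 1 − 2ρ²/(1 + ρ) if all correlations equal ρ; 1 − r² under AR(1) (r₁₂ = r₂₃ = r, r₁₃ = r²), because arrival adds nothing once the pre-walk sample is known

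| Pattern | r | Change, arrival | Change, pre-walk | Change, mean | Covariate: arrival | Covariate: pre-walk | Both covariates |
|---|---|---|---|---|---|---|---|
| Equal | 0.4 | 1.20 | 1.20 | 0.90 | 0.840 | 0.840 | 0.771 |
| Equal | 0.8 | 0.40 | 0.40 | 0.30 | 0.360 | 0.360 | 0.289 |
| AR(1) | 0.5 | 1.50 | 1.00 | 1.00 | 0.938 | 0.750 | 0.750 |
| AR(1) | 0.7 | 1.02 | 0.60 | 0.66 | 0.760 | 0.510 | 0.510 |
| AR(1) | 0.9 | 0.38 | 0.20 | 0.24 | 0.344 | 0.190 | 0.190 |

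With equal correlations, the second covariate cuts residual variance by 8% (0.771/0.840 = 0.92) to 20% (0.289/0.360 = 0.80). Under AR(1) the gain is zero against the pre-walk sample, and 20% to 45% against arrival alone (0.750/0.938 = 0.80; 0.190/0.344 = 0.55). Averaging the two samples helps under equal correlations but under AR(1) gives no gain or a loss against the pre-walk sample (0.66 v 0.60 at r = 0.7). The two-covariate model is never worse than any of these, apart from a degree of freedom, because each is a restricted version of it.

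**The case against.** The strongest reply is that the stated t1 is simply before the walk, which the second sample fits exactly. Baseline stress level is then a descriptive phrase in Procedures and not an analysis definition, and handling of repeated baselines is commonly left to an analysis plan. Fig. 2, which is not shown, may also label the samples. Much of this stands: the point is an ambiguity, not a proven error. But the article prints one model for all outcomes, and that model does not settle the question for an outcome sampled three times.

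A reader might infer more than the text supports:
- *That one sample must be discarded.* No passage says so, and a before/after mixed model accepts two before rows per person. A trial fit on one simulated data set ran with 240 rows (SE 0.157) against 160 rows with one (SE 0.168). Pooling does, however, treat the two samples as equivalent.
- *That the change would include the journey.* The first sample is taken after arrival, so it does not.
- *That H1–H4 are biased.* All conditions follow the same procedure, and a common battery effect cancels. A difference is conceivable: allocation precedes attendance, the battery is done at the assigned site, Table 2 route levels run from 48.74 to 68.71 dBA, and the Background cites raised cortisol during a cognitive task in louder surroundings. Those comparisons were 90 against 45–60 dBA, and levels at the starting points are not reported.
- *That a fixed share of precision is lost.* That depends entirely on the unknown correlations.

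It is also fair that there is no non-walking arm and that cortisol varies over the day, so even the best baseline does not isolate the walk within a condition.

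**Conclusion.** The point holds as an unresolved definition for a co-primary outcome, worth correcting but not a demonstrated bias. The protocol does not name the before value for cortisol, and its only baseline label points to a sample that precedes the battery. Used alone, that sample would add the battery to any within-condition change, including the abstract's promised effect of walking in general. H1–H4 are safe if the battery response is the same at all sites, and shift by up to δ if it is not; nothing in the document gives δ. Using both samples as covariates lowers residual variance by about 8–20% against a single covariate if correlations are equal at 0.4–0.8, and by as little as zero against the pre-walk sample under AR(1).

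**What to change.** - For cortisol, model the post-walk sample on vegetation, noise and their interaction, with the arrival and pre-walk samples as two separate covariates and a random intercept for group. With one outcome row per person, the subject intercept drops out.
- For any within-condition walk change, use the sample taken directly before the walk, not the arrival sample or the mean of the two.
- Reword the arrival sample in Procedures so that it is not presented as the sole baseline, and state the role of each sample.
- Report the arrival-to-pre-walk change by condition. The covariate model does not fully remove a site-dependent battery effect: if δ persists to the post-walk sample, it leaves (1 − β)δ, where β is the coefficient of the pre-walk sample. If this change differs between conditions, show the contrast in change from the pre-walk sample as a sensitivity analysis.

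The cost is one extra model term and a few sentences. No new samples are needed.

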**Fig. 1 Fig1:**
[figure not shown]
Audio recording

Participants will be asked to walk in silence and not to outpace the experimenter. After the walk, a third cortisol probe will be taken, the attention test will be conducted again, and participants will be asked to respond to the post-questionnaire. For an illustration of the study procedure, see Fig. 2.

**Fig. 2 Fig2:**
[figure not shown]
Study procedure

Data will be collected in three waves: May to October 2022, August to October 2023, and in a third wave in 2024. Any substantial protocol modifications will be communicated to *BMC Psychology* and approved by the ethics committee.

### Outcomes

#### Primary outcomes

The primary outcomes are “perceived restoration”, measured with a self-report questionnaire and salivary cortisol as a physiological stress marker.

Perceived restoration will be assessed using a slightly modified version of the restoration outcome scale (ROS) [67]. The questionnaire was put in past tense, and participants will be asked to what extent the walk contributed to three items concerning relaxation and calmness (e.g., “I feel calmer after being here”), one item reflecting attention restoration (“my concentration and alertness clearly increased”), and two items indicating clearing one’s thoughts (e.g., “I was able to forget my everyday worries here”). The questionnaire has been translated into German, including a back translation into English by the internal translator of the Swiss Federal Research Institute WSL. Items are rated on a Likert scale ranging from 1 (*not at all*) to 7 (*completely*). The scale has been used in several previous studies examining the benefits of exposure to nature [14, 68, 69] and has been shown to have good internal consistency with a Cronbach’s alpha of .92 [67].

The physiological stress marker salivary cortisol is considered a reliable indicator for assessing hypothalamic pituitary adrenocortical (HPA) axis activity [62, 70]. Saliva samples will be collected using synthetic swabs (Sarstedt, Germany). For saliva collection, participants will place the swab in their mouth for 2 min before returning it to the salivette collection tube. The salivettes will be put in a portable cooler immediately after saliva collection and stored there until the end of the walk. When returning from the field, saliva samples are frozen and stored at − 20 °C until analysis. The samples will be analyzed by the laboratory of [name]. [name] at the Technical University of Dresden, Germany, to determine cortisol levels. After thawing, the samples will be centrifuged at 3,000 rpm for 5 min to obtain a clear supernatant of low viscosity. Salivary concentrations are measured using a commercially available chemiluminescence immunoassay with high sensitivity (Tecan – IBL International, Hamburg, Germany; catalog number R62111).

#### Secondary outcomes

Self-report questionnaires

*Affect*

Positive and negative affect will be assessed using the Positive and Negative Affect Schedule [71]. It consists of 20 items, providing separate scores for a positive affect scale (10 items, e.g., “active” and “enthusiastic”) and a negative affect scale (10 items, e.g., “nervous” and “distressed”). Items are rated on a 5-point Likert scale ranging from 1 (*not at all*) to 5 (*extremely*). Participants will be asked to indicate the extent to which they currently experience each of the feelings or emotions. The scale has been widely used in previous studies examining the benefits of exposure to nature and has been shown to be sensitive to change in this context [14, 15, 72–74]. A good internal consistency of the scale, with a Cronbach’s alpha of between .86 and .90 for positive affect and between .84 and .87 for negative affect, has been reported [71].

*Rumination*

Rumination will be assessed using the German version of the Perseverative Thinking Questionnaire (PTQ; [75]). The PTQ measures content-independent repetitive negative thinking (RNT), which is referred to as rumination in research [76]. For 15 statements related to their process of thinking, the participants will rate how often they apply to them using a 5-point Likert scale ranging from 0 (*never*) to 4 (*almost always*). Item examples of RNT are: “The same thoughts keep going through my mind again and again”, or “Thoughts come to my mind without me wanting them to.” The internal consistency and convergent validity of the PTQ have been shown to be good [75]. The PTQ was evaluated in nonclinical and clinical samples and shown to have a high internal consistency of Cronbach’s alpha = .94 for the nonclinical sample [75].

*Nature relatedness*

Nature relatedness will be measured with the 6-item short form of the Nature Relatedness Scale (NR-6; [77]). The construct of nature relatedness [76] is assumed to capture an individual’s interest in nature, fascination with nature, and desired contact with nature. Nisbet and Zelenski [77] understand nature relatedness as encompassing an awareness and understanding of all aspects of the natural world, transcending aesthetically appealing aspects. In the present study, we will apply the German version [78] of the NR-6 (e.g., “I always think about how my actions affect the environment,” “My relationship to nature is an important part of who I am,” and “My ideal vacation spot would be a remote, wilderness area”). The scale encompasses the affective and cognitive elements of the relationship with nature. Participants will be asked to respond to the items on a 5-point Likert scale ranging from 1 (*strongly disagree*) to 5 (*strongly agree*). The NR-6 scale has been shown to have good internal consistency, with a Cronbach’s alpha between .83 and .86 [77].

*Connection to nature*

Connection to nature will be assessed using the Love and Care for Nature Scale (LCS; [79]). The LCS measures the emotional components of the connection between humans and nature with reference to the two terms love and care for nature. The initial version of the LCS was developed by Perkins [79]. Perkins defines the construct of love and care for nature as “deep love and caring for nature which includes a clear recognition of nature’s intrinsic value as well as a personal sense of responsibility to protect it from harm” [79]. The LCS was chosen due to its affective focus on the relationship with nature. In the present study, we will use the 5-item version of the scale. Items (e.g., “I feel a deep love for nature”) are rated on a 7-point Likert scale ranging from 1 (*strongly disagree*) to 7 (*strongly agree*). The scale has been shown to have good internal consistency, with a Cronbach’s alpha of .93 [79].

*Satisfaction with life*

Life satisfaction will be measured with the German General Life Satisfaction Short Scale (L-1; [80]); for the English version see Nießen an colleagues [81]). This constitutes a single item (“How satisfied are you at present, all in all, with your life?”), rated on an 11-point scale (0 = *not satisfied at all* to 10 = *completely satisfied*). A good test–retest reliability as well as high convergent validity with other multi-item scales measuring satisfaction with life have been shown for the L-1 [80].

*Perceived restorative qualities of environments*

The extent to which the different environments examined in this study have restorative qualities will be assessed using the Perceived Restorativeness Scale-11 (PRS-11) [82]. Pasini et al. [82] established an 11-item version of the scale, favoring a four-factor model with the factors “being away,” “fascination,” “coherence,” and “scope.” Results have shown the PRS-11 to discriminate among different environmental categories, with hills and lakes exhibiting the highest PRS scores and industrial zones holding the lowest scores [82]. The questionnaire has been translated into German, including a back translation into English by the internal translator of the Swiss Federal Research Institute WSL. Subjects rate the extent to which the items reflect their experience of the environment in which they have been walking with higher sum scores, indicating stronger perceived restorativeness. Information on the internal consistency for this scale is not available.

*Stress recovery*

In an additional question, using a 7-point Likert scale, ranging from 1 (*not at all*) to 7 (*completely*), participants indicated to what extent the environment they walked through contributed to them being able to recover from stress.

*Noise annoyance*

Noise annoyance will be assessed with the 11-point International Commission on Biological Effects of Noise (ICBEN) [83], also recommended in Standard ISO/TS 15666 [84], assessing per noise source how much the participants felt bothered, disturbed, or annoyed by noise from the corresponding sources during the walk (road traffic noise, public transport, railway noise, aircraft noise, construction work noise, or noise from restaurants, bars, or leisure activities). Items are rated on a Likert scale ranging from 0 (*not at all*) to 10 (*extremely*). The scale is a standardized noise annoyance scale widely used in noise annoyance research, yielding internationally comparable measures of annoyance reactions in noise studies [83].

*Acoustic impression of the soundscapes*

The participants’ individual experience of soundscapes will be assessed in accordance with the International Organization for Standardization data collection and reporting requirements ISO/TS 12913–2 [85]. Participants will rate the extent to which the soundscape during the walk was perceived as pleasant, chaotic, vibrant, uneventful, calm, annoying, eventful, and monotonous on a 5-point Likert scale ranging from 1 (*not at all*) to 5 (*completely*). Additionally, we added “loud” as a ninth attribute to rate on the same scale. Following ISO/TS 12913–2 [85], participants will further be asked to rate to what extent they heard the four following types of sounds during the walk: “traffic noise (e.g., cars, buses, trains, and airplanes),” “other noise (e.g., sirens, construction, industry, and loading of goods),” “sounds from human beings (e.g., conversation, laughter, children at play, and footsteps),” and “natural sounds (e.g., singing birds, flowing water, and wind in vegetation)”. Items will be rated on a 5-item Likert scale, ranging from 1 (*not at all*) to 5 (*dominates completely*). In addition, participants will be asked to rate the overall sound environment during the walk on a 10-point Likert scale, ranging from *very pleasant* to *very unpleasant*.

*Demographics*

We will assess age, gender, highest education, main occupation, income, frequency of exposure to nature, previous mindfulness experience, and noise sensitivity. Noise sensitivity will be evaluated with one item, asking participants how strongly they agree with the statement “I am noise sensitive”. The item is rated on a 5-point rating scale ranging from 1 (*do not agree at all*) to 5 (*very much agree*). The approach to assess noise sensitivity with a single question was taken from Brink et al. [86], who introduced this concept. Furthermore, we will ask the participants to describe their emotions through the sounds they heard during the walk. Finally, they will be asked to what extent going for a walk helps them think through personal problems and how their thoughts change when they go for a walk.

Physiological outcome measure

*Skin conductance*

Skin conductance level (SCL) will be measured continuously throughout the experiment with Shimmer3 GSR + sensor wristbands [87]. Electrodes will be placed on the volar phalanges of two fingers of the non-dominant hand. In previous research, SCL was shown to be an effective indicator of physiological stress, and SCL variations reflect changes in arousal [88].

Cognitive test

*Attention*

Attention will be assessed with the Necker Cube Pattern Control Test [65, 66], subsequently referred to as the Necker Cube Test. Stevenson et al. [89] and Ohly et al. [90] identified cognitive domains sensitive to restorative processes through exposure to greenspaces. According to Stevenson et al. [89] measures of attention control might exhibit the most direct relation to effortful directed attention. Here, different tests assessing attention control were explored, and the Necker Cube Test was selected [65]. The Necker Cube Test is a three-dimensional wire frame drawing of a cube without depth cues, which can be seen from two different perspectives [65]. When observed for more than a few seconds, the cube spontaneously switches perspectives due to reversals of the fore- and background [65]. It is assumed that holding one perspective and avoiding reversals requires directed attentional capacities [65]. After having been familiarized with the functionality of the paper version of the test, the participants are instructed to hold one perspective as long as they can and indicate every time the pattern reverses. Changes in perspective occurring despite attempting to focus on one pattern are believed to rely on attentional fatigue [35]. The number of reversals is thus used as a measure for directed attention, with fewer shifts indicating better attention.

